### Inclusion and exclusion criteria

#### *Inclusion criteria*

- At least 18 years of age
- Being a healthcare worker exposed to respiratory disease due to COVID-19: medical personnel, chemists, nurse practitioners, cleaning staff, stretch workers, transportation workers, administrative personnel and respiratory therapy; with training in biosecurity measures and proper use of respiratory protection equipment to lower the risk of COVID-19.
- Absence of respiratory symptoms at the randomization and start of treatment/placebo.
- Informed consent, including randomization to any group.

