## **Definition of the Problem**

Healthcare personnel have a high risk of COVID-19 infection (1). In China, until the beginning of March, more than 3300 COVID-19 infections in medical staff have been reported, and in some hospitals such as Clinic Barcelona 23% of physicians have contracted COVID-19. In Italy, the estimated incidence of COVID-19 is similar, with 20% of medical staff infected (1). Another severe problem is that healthcare workers may take the COVID-19 infection to their homes, having transmission to their family members been reported; besides, personnel might be an in-hospital vector, spreading the infection to patients being treated for other causes, or to the rest of the medical team.

Disease in healthcare personnel is an extremely severe problem in health emergencies, since it limits capacity of attention, weakens the workforce and diminishes motivation. In fact, in China 40,000 physicians were mobilized from other regions to support Wuhan and its province in the initial outbreak. Moreover, in Italy, news of hiring physicians from other countries like Cuba, China and Venezuela to support medical care of affected patients spread, since health systems were overwhelmed.

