### *Main outcome*

Symptomatic infection (dry cough with or without dyspnea, with or without fever) due to COVID-19 proved via PCR-TR according to the OMS protocol.

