#### *Ending of recruitment*

#### *Tests to perform*

- Minimum tests at recruitment (before randomization) and at 30 and 60 days:
  - Blood count
  - Serum electrolytes
  - Blood chemistry (3 elements): to quantify the effects on blood sugar and rule out type 2 diabetes mellitus at baseline.
  - Hepatic profile
  - Electrocardiogram: to evaluate the incidence of heart conduction alterations.
- 10-respiratory virus and SARS-CoV-2 panel, only in case of symptoms.

At 30 and 60 days: surveillance of adverse events.

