#### Necessary number of subjects

#### *Significance level*

5% alpha at two tails.

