#### *Exclusion criteria*

- Known hypersensitivity to HCQ, evidenced by anaphylaxis.
- Current treatment with HCQ or chloroquine.
- Weight less than 50 kg at the basal evaluation.
- Women with last menstrual date a month before recruitment without a pregnancy test.
- Women with positive pregnancy test.
- Lactating women.
- History of chronic hepatic disease (Child-Pugh B or C)
- History of chronic kidney disease (GFR lower or equal to 30)
- History of treatment with tamoxifen.
- History of retinopathy of any cause, and/or loss of central vision, loss of nocturnal visual acuity, blurred vision and alteration of color vision.

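### Workers with earlier PCR-confirmed COVID-19 are not excluded and the outcome need not be a new infection, which may cost power without favouring either arm

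*Protocol*

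**What the plan says.** - **Protocol, Inclusion criteria.** Besides age, an exposed job with biosecurity training, and consent, the protocol asks for "Absence of respiratory symptoms at the randomization and start of treatment/placebo". This is the only criterion that touches infection status.
- **Protocol, Exclusion criteria.** The ten items concern hypersensitivity, drug use (for example "Current treatment with HCQ or chloroquine"), weight, pregnancy (two items), lactation, liver, kidney, tamoxifen and the retina. None concerns previous or current COVID-19.
- **Protocol, Tests to perform.** Under "Minimum tests at recruitment (before randomization) and at 30 and 60 days" the list is blood count, electrolytes, blood chemistry, hepatic profile and electrocardiogram. Virus testing is separate: "10-respiratory virus and SARS-CoV-2 panel, only in case of symptoms".
- **Protocol, Main outcome.** "Symptomatic infection (dry cough with or without dyspnea, with or without fever) due to COVID-19 proved via PCR-TR according to the OMS protocol". Nothing requires a negative starting state or an infection acquired after randomisation.
- **Protocol, Elimination criteria and Statistical analysis.** The only elimination criterion is withdrawal by the participant or a legal representative. All randomised subjects enter the intention-to-treat analysis.
- **Protocol, Definition of the Problem.** At one hospital in Barcelona "23% of physicians have contracted COVID-19", and a similar figure of 20% of medical staff is given for Italy.

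**The concern.** The research question and hypothesis are about the incidence of symptomatic infection, and the sample size applies one event rate to everybody enrolled. Both work best if participants are at risk of a new event when they are randomised. The staff to be recruited already care for COVID-19 patients, so some may have had the disease before entry, and the criteria would let them in.

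Two things could follow. If recovered workers are at lower risk, they take up places and add few events. If a recovered worker still sheds detectable virus and later develops a cough for another reason, the PCR could turn an old infection into an outcome that study drug had no chance to prevent. Either would reduce the trial's ability to show an effect that exists. Eligibility and the outcome definition belong in the protocol, so an unseen analysis plan would not be expected to close the gap.

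**Working it through.** **1. Is the gap closed anywhere?** Take a worker with PCR-confirmed COVID-19 some weeks ago who is now free of respiratory symptoms. The inclusion criteria are met, no exclusion applies, no baseline test would show the earlier infection, no elimination criterion removes the worker, and the analysis keeps everyone randomised. The gap is open at each step.

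**2. Inputs for its size** (Protocol, Necessary number of subjects)
- COVID-free survival of 76% on control, with a 10-point gain read as 86%. The event risks are 24% and 14%, which sum to 0.38.
- "5% alpha at two tails"; stated power 90%.
- 159 per group calculated, 200 per group enrolled to allow for losses (159/200 = 79.5%, so an implied loss of 20.5%).
- Hazard ratio under proportional hazards: ln 0.86 / ln 0.76 = 0.550, so |ln HR| = 0.599.

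**3. The plan's own figure.** Schoenfeld events for 90% power: d = 4 × (1.960 + 1.282)² / 0.599² ≈ 117.3, rounded up to 118. Then n = 118 / 0.38 ≈ 311 per group. Freedman's formula gives 125 events and 329 per group. The stated 159 per group does not reproduce. That is a separate matter, but it means the power below starts well under 90% before any dilution.

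**4. Dilution.** Let s be the share of each group with earlier infection. **Assumption:** these workers have no events, which is the upper bound on dilution for a given s. Then

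- expected events d = n × (1 − s) × 0.38
- power = Φ(√d / 2 × 0.599 − 1.960)

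| Share s (assumed) | Events, n = 200, no losses | Power | Events, n = 159 | Power |
|---|---|---|---|---|
| 0% | 76.0 | 74% | 60.4 | 64% |
| 5% | 72.2 | 72% | 57.4 | 62% |
| 10% | 68.4 | 70% | 54.4 | 60% |
| 20% | 60.8 | 65% | 48.3 | 55% |

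Example for n = 159 and s = 20%: d = 159 × 0.8 × 0.38 = 48.3; √48.3 / 2 × 0.599 = 2.081; 2.081 − 1.960 = 0.121; Φ = 0.548.

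The table holds the hazard ratio at 0.55. Recomputing it from the diluted risks moves it slightly (0.557 at s = 20%) and lowers power by about two further points at most: to 63% with 200 and 53% with 159 per group. The conclusion is the same.

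**5. Old infections counted as events.** The documents give no rate, so this is only an illustration. Suppose a fraction g of each arm is counted as an event whatever the treatment. The risks become 0.24 + 0.76g and 0.14 + 0.86g. At g = 2% they are 25.5% and 15.7%, and the apparent hazard ratio is 0.58. At g = 5% they are 27.8% and 18.3%, and it is 0.62. With 159 per group, power goes from 64% to 60% or 53%.

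**The case against.** The strongest reply is that the harm depends on facts the protocol does not contain.

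- **Protection after infection.** Nothing in the document says a recovered worker is protected. This stands: zero events is a ceiling on dilution, not an expectation.
- **Share at entry.** A reader might infer from the 20% and 23% quoted for Italy and Barcelona that about a fifth of this institute's staff had already been infected. The documents do not support that. The figures come from elsewhere, the background describes an early stage of the epidemic, and recruitment was to begin straight after approval. At 5% the loss is about two points of power.
- **Old infections as outcomes.** A reader might infer that earlier infections will be counted as events. That needs a worker who has no respiratory symptoms at entry, later develops a dry cough, and is still PCR-positive from the old illness. It is possible under the outcome definition, but no rate is given. The ten-virus panel done at the same time may also point to another cause.
- **First infections.** The research question concerns symptomatic COVID-19 in exposed staff and is nowhere limited to first infections, so enrolling all exposed staff is not a contradiction. This also stands. The point is that the choice costs power and has not been addressed.
- **Bias.** A reader might infer that the comparison is tilted towards one arm. It is not: randomisation balances earlier infection on average, and both mechanisms act towards no difference.

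None of this closes the gap in eligibility. It limits how much can be claimed for it.

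**Conclusion.** The point holds as an eligibility gap with a modest and uncertain cost in power. The protocol admits recovered, symptom-free workers and keeps them in the main analysis. Under the upper-bound assumption of no events among them, the loss is about 2 points of power at a 5% share, 4 to 5 points at 10%, and 9 to 10 points at 20%, whether counted on 200 or on 159 per group. The base of 200 assumes no losses. The base of 159 is nearer to what the protocol itself expects to be evaluable. The true share at this site is unknown, and the miscounting of old infections is a possibility without a rate.

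The change is worth making because it is cheap and the trial has no spare power: about 64% to 74% on its own inputs against the stated 90%. It is not a flaw that invalidates the comparison, and the shortfall in the sample size calculation is the larger power problem.

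**What to change.** Add one line to the Exclusion criteria: previous PCR-confirmed COVID-19, established by history and from existing staff records, with no new test. If any such worker has already been randomised, keep that person in the intention-to-treat set and add a sensitivity analysis of the main outcome without them.

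**Cost:** one eligibility line, one screening question and one extra analysis. A few willing workers become ineligible.

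**What it does not do:** history and records will miss infections that were never diagnosed or are still incubating at entry, so some dilution and some risk of miscounting remain.

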#### *Exclusion criteria*

- Known hypersensitivity to HCQ, evidenced by anaphylaxis.
- Current treatment with HCQ or chloroquine.
- Weight less than 50 kg at the basal evaluation.
- Women with last menstrual date a month before recruitment without a pregnancy test.
- Women with positive pregnancy test.
- Lactating women.
- History of chronic hepatic disease (Child-Pugh B or C)
- History of chronic kidney disease (GFR lower or equal to 30)
- History of treatment with tamoxifen.
- History of retinopathy of any cause, and/or loss of central vision, loss of nocturnal visual acuity, blurred vision and alteration of color vision.

#### *Elimination criteria*

- Decision from the participant or their legal representative to withdraw from the study

### Statistical analysis

Categorical variables will be described with frequencies and percentages, numerical variables with mean and standard deviation or median and interquartile range according to their distribution. The time to the outcome (COVID-19) and to the compound outcome will be estimated, in both the experimental and the placebo group. The survival function will be estimated with the Kaplan – Meier method and the log rank hypothesis test will be used to contrast the time to outcome in each study group. The hazard ratio and its 95% confidence interval will be used as measure of association strength to evaluate the effect of the prophylactic HCQ over the main and secondary outcomes of the study. The effect of prophylaxis on both proposed

study strata will be estimated with the log rank test, and the interaction prophylaxis – strata will be evaluated with Cox regression. Due to the urgency of knowing the study results, the following interim analysis are proposed: at the moment that the 50% of the sample has had a follow-up of four weeks and at the moment that 50% of the sample has had 8 weeks of follow-up. The subjects that do not present the outcome will be censored in their follow-up at three months from the random allocation and start of the intervention (HCQ/placebo). We propose a multivariate Cox analysis to evaluate the risks associated with COVID-19 and risk of the composite outcome. All analysis will be two-tailed, the analysis strategy is intention to treat, and all randomized subjects will be included in the analysis.

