#### *Randomization*

Healthcare workers exposed to patients with COVID-19 diagnosis will be distributed randomly in a stratified way. The strata for randomization will be the following:

- a) Group A: subjects with high-risk exposition to COVID-19; defined as the personnel who perform high risk invasive procedures (bronchoscopy, intubation, extubation and/or respiratory sample taking), care of critical or under mechanical ventilation patient.
- b) Group B: subjects with low to moderate risk exposition to COVID-19; defined as the personnel who attend patients in triage or outpatient areas, or whose participation in the Unit corresponds to cleaning or administration labour.

The randomization distribution will be performed with the permuted block method with random allocation, in blocks of four pairs.

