#### *Power*

(1-beta, possibility of detection): 90%

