### *Final calculation*

According to the proposed statistical analysis, the difference in time to outcome will be performed with a log-rank test, using the following formulas:

$$n = \frac{d}{2 - S1(\infty) - S2(\infty)} \text{ y } d = (Z\alpha(2) - Z1 - \beta)^2$$

Considering a difference of 10% of higher survival rates free of COVID-19 and considering a reported survival rate free of COVID-19 of 76%, a sample size of 159 per group is obtained. Considering the losses, it is decided that 200 subjects will be included per group, for a total of 400 subjects.

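### Randomisation is stratified by exposure group A/B, but the primary log-rank test and hazard ratio are specified without that factor: valid but conservative, at a small and avoidable cost in power

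*Protocol*

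**What the plan says.** Protocol, Randomization: "Healthcare workers exposed to patients with COVID-19 diagnosis will be distributed randomly in a stratified way". Group A covers staff who perform high-risk invasive procedures or care for critical or ventilated patients. Group B covers triage and outpatient staff, cleaners and administrators. Allocation is by permuted blocks.

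Protocol, Statistical analysis: after Kaplan-Meier estimation, the "log rank hypothesis test will be used to contrast the time to outcome in each study group". The HR with its 95% confidence interval is the measure of effect. Neither statement mentions Group A/B. The strata appear in the next sentence, where the effect of prophylaxis on both "study strata will be estimated with the log rank test" and the prophylaxis-by-strata interaction is assessed by Cox regression. A multivariate Cox analysis is also proposed, with no covariates listed.

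Protocol, Final calculation: the trial is sized on the basis that "the difference in time to outcome will be performed with a log-rank test", again with no stratum term.

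**The concern.** The two strata are defined by expected infection risk, so the design anticipates that they differ in prognosis. Blocking within them makes the arms nearly equal in their mix of A and B, and this removes one source of chance difference between the arms. An overall log-rank test that ignores the strata still counts that source in its variance. Its standard error is then too large for the design, so the test rejects less often than it should, both under the null and under the alternative.

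The HR is affected too. When baseline hazards differ between strata, the HR from a model without the factor lies nearer 1 than the HR within each stratum.

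At stake is some efficiency, and clarity about which HR is reported. The choice of test also matters because the protocol plans interim looks that may lead to unblinding or stopping, so the test should be fixed before any look.

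**Working it through.** **Inputs from the protocol.** Significance level: "5% alpha at two tails". Power: 90%. COVID-free survival without prophylaxis: 76% (Final calculation). Effect: "Considering a difference of 10% of higher survival rates free of COVID-19", read as 86% against 76%. Enrolment: 200 per group. Implied HR = ln(0.86)/ln(0.76) = 0.1508/0.2744 = 0.550.

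**Not given, so assumed.** The share of subjects in Groups A and B and the event risk in each.

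**The plan's own figure.** The protocol states 159 per group. Its form n = d/(2 − S1 − S2) has denominator 0.24 + 0.14 = 0.38.
- Schoenfeld: d = 4 × 10.507/(ln 0.550)² = 42.03/0.3583, rounded up to 118 events; n = 118/0.38 = 311 per group.
- Freedman: d = 10.507 × (1.550/0.450)², rounded up to 125 events; n = 125/0.38 = 329 per group.

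So 159 is not reproduced. At 200 per group, 76 events are expected (200 × 0.38). Power is then 74% by Schoenfeld (√76 × 0.5986/2 − 1.960 = 0.65) and 72% by Freedman or by two proportions. This is a separate matter, and it sets the baseline for what follows.

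**Type I error by hand.** Take equal strata with mean risk 24%. The pooled variance of the outcome is 0.24 × 0.76 = 0.1824. With arms balanced inside strata, only the within-stratum variance contributes to the difference between arms. A test using the pooled variance has true size 2 × [1 − Φ(1.960/√ratio)], where ratio = within/pooled.

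| Risk A / B | Hazard ratio A:B | Within-stratum variance | Ratio | True size |
|---|---|---|---|---|
| 30% / 18% | ln 0.70/ln 0.82 = 1.8 | (0.2100 + 0.1476)/2 = 0.1788 | 0.980 | 4.8% |
| 34% / 14% | ln 0.66/ln 0.86 = 2.8 | (0.2244 + 0.1204)/2 = 0.1724 | 0.945 | 4.4% |
| 40% / 8% | ln 0.60/ln 0.92 = 6.1 | (0.2400 + 0.0736)/2 = 0.1568 | 0.860 | 3.5% |

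Simulated log-rank tests agree: 4.5%, 4.3% and 3.5% unstratified, against about 5% stratified.

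**Power by simulation.** Settings: 200 per arm, equal strata, exponential hazards, within-stratum HR 0.55. Two separate sets of runs:

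| Risk A / B | Set 1: unstratified / stratified | Loss (points) | Set 2: unstratified / stratified | Loss (points) |
|---|---|---|---|---|
| 30% / 18% | 71.6% / 72.1% | 0.5 | 72.7% / 73.5% | 0.8 |
| 34% / 14% | 71.4% / 72.9% | 1.5 | 71.2% / 73.1% | 1.9 |
| 40% / 8% | 68.8% / 73.6% | 4.8 | 69.7% / 73.9% | 4.2 |

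The one-step HRs, unstratified against stratified, were 0.564 against 0.556 (34%/14%) and 0.576 against 0.555 (40%/8%). The shifts are 0.008 and 0.021.

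**Sensitivity to the set-up.** A second model holds overall survival at 76% against 86% and lets the within-stratum HR move. At 200 per group:

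| Group A share | Hazard ratio A:B | Power, unstratified to stratified | Within-stratum HR / marginal HR |
|---|---|---|---|
| 50% | 2 | 73.2% to 73.9% | 0.546 / 0.549 |
| 50% | 3 | 73.9% to 75.6% | 0.541 / 0.549 |
| 50% | 5 | 74.4% to 77.6% | 0.532 / 0.549 |
| 50% | 10 | 75.2% to 80.3% | 0.522 / 0.549 |
| 30% | 3 | 73.2% to 75.9% | 0.538 / 0.549 |
| 30% | 10 | 76.3% to 85.1% | 0.497 / 0.548 |

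The two models agree in direction and order of size. The loss is about 3 points or less up to a hazard ratio of 3, and larger only when the strata differ strongly.

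**The case against.** The strongest reply is that the protocol never calls the primary test unstratified. It leaves the point open, the strata are used elsewhere in the same section, a Cox interaction model would ordinarily carry the stratum main effect, and the multivariate Cox model might include exposure group. A SAP that is not shown could settle it. This stands in part. A reader might infer that the protocol has decided on an unstratified analysis, and the text does not go that far. But it names the overall test and the effect measure, says separately what the strata are for, and gives them only subgroup and interaction roles. The multivariate model is aimed at risks associated with COVID-19 and is not named as the treatment comparison. The natural reading is an ordinary two-group test.

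A second reply is that the HR is not biased. This stands. The HR is non-collapsible, so the marginal and within-stratum HRs are different quantities. One nearer 1 is not a faulty estimate of the other, and the protocol does not say which it wants.

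A third is that the size of the loss rests wholly on assumed strata. This also stands. A ratio near 6 or 10 has no figure in the protocol behind it. It cannot be ruled out either, since Group A intubates and cares for ventilated patients while Group B includes administrators.

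**Conclusion.** The design and the stated primary analysis do not match, and the protocol should reconcile them. If analysed as written, the overall comparison is valid but conservative: type I error is about 4.5% for modest differences between strata and about 3.5% for a large one. The HR is a marginal one, nearer 1 by about 0.01 to 0.02 in the 34%/14% and 40%/8% scenarios. With equal strata and 200 per arm, the power loss is about 0.5 to 2 points for risks of 30%/18% to 34%/14%, and 4 to 5 points for 40%/8%. Under the second model it reaches 5 to 9 points only at a hazard ratio of 10.

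Two stronger readings are not supported. A reader might infer that omitting the strata makes the trial's conclusion unsafe. It does not, because the error is on the conservative side. A reader might also infer that it explains why power falls short of 90%. It does not: the 72 to 74% at 200 per group comes from the sample size calculation, and no scenario computed reaches 90% by stratifying (the highest is 85.1%). The point is an improvement worth making, not a flaw that invalidates the analysis.

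**What to change.** In Protocol, Statistical analysis, state that the primary log-rank test, at each interim and at the final analysis, is stratified by randomisation stratum (Group A/B), and that the primary HR with 95% confidence interval comes from a Cox model stratified by the same factor. Keep the per-stratum results and the prophylaxis-by-strata interaction as secondary.

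The cost is one sentence of wording. Exposure group is already recorded for every subject at randomisation, so no new data or subjects are needed. The wording should be settled before the first interim look. The sample size in Final calculation needs its own correction.

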#### *Experimental group*

Subjects in this group will receive HCQ orally, 200 mg/day for 60 days. According to the result of the interim analysis at 4 and 8 weeks it will be decided whether to remove the blind and giving the prophylaxis to both groups or not. According to the results of the trial, an amend may be made to continue with an open label study, studying prophylaxis with HCQ.

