#### *Data and security monitoring committee (DSMC)*

A DSMC will take part in the study, being a multidisciplinary advisor group formed by a biostatistics expert, a clinical researcher, an ethics expert and a clinician involved with influenza and coronavirus, none of whom will be involved in the clinical trial and are therefore independent, who, at proposed times, will have access to the data and randomization list so that they can evaluate the data including security and outcomes.

Clinical researcher: [name], clinical pharmacologist, anesthetist and intensivist who will act as coordinator.

Statistician: MSc [name], Chief of the Epidemiologic Department, INER.

Ethics: [name] [name], Medical Director, INER.

Clinician: [name], specialist in Infectious Diseases, expert in influenza-like infections and now in COVID-19.

Their goal will be to evaluate advantages and disadvantages of continuing the trial having recruited half the proposed sample size, above all if it is considered ethical to continue recruitment, given the outcomes found at this time. At this moment there are not controlled studies to compare this with, but they may be made public during the study.

An interim analysis is planned when half the sample is completed, so that a noticeable difference may be identified in the main outcome, which may show an advantage in effectiveness, that for its magnitude forces the trial to stop. Adverse events or toxicity will also be watched for. The final statistical analysis will be made considering this intermediate analysis. }

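### The protocol gives two conflicting interim schedules for efficacy and no boundary; if each look were tested at 5%, overall type I error would be about 8% with one interim and 9 to 11% with two

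*Protocol*

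**What the plan says.** **Schedule with two interims.** Protocol, Statistical analysis: the first interim comes "at the moment that the 50% of the sample has had a follow-up of four weeks", the second when half the sample has eight weeks. Protocol, Experimental group, attaches a decision to these looks: "According to the result of the interim analysis at 4 and 8 weeks it will be decided whether to remove the blind" and give prophylaxis to both groups. Ethical considerations repeats the timing: if benefit is clear, an amendment to unblind would be proposed at week 4, at week 8 or at the end of the three months.

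**Schedule with one interim.** Protocol, Data and security monitoring committee (DSMC): "An interim analysis is planned when half the sample is completed, so that a noticeable difference may be identified in the main outcome". The section adds that an advantage may be large enough to force the trial to stop. A paragraph earlier it places the committee's judgement at the point where half the planned sample has been recruited.

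**Error rate.** Protocol, Significance level: "5% alpha at two tails". Statistical analysis adds: "All analysis will be two-tailed". The only remark on adjustment is the last sentence of the DSMC section, which says that the final analysis will take the intermediate analysis, in the singular, into account.

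**Follow-up.** Subjects without the outcome are censored at three months from randomisation, and the analysis is by intention to treat.

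**The concern.** The sections disagree on how many efficacy looks there are (two or one) and on what triggers them. The DSMC section also disagrees with itself on the trigger. A committee working from this text could not tell when to look or how often.

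These are efficacy looks with consequences, because the outcome can be unblinding or stopping for benefit, and unblinding cannot be undone. The criteria are verbal only: a difference that is noticeable, its magnitude, or a benefit that is clear. Repeated looks at an accumulating log-rank statistic raise the chance of a false positive unless the levels are set jointly. The stated intention to adjust covers fewer looks than the Statistical analysis section plans.

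A linked gap is what happens after unblinding. If placebo subjects are then offered HCQ, the protocol does not say whether their later time counts in the primary comparison under three-month intention-to-treat follow-up.

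**Working it through.** **1. The schedules side by side**

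| Section | Interim looks | Trigger | Possible consequence |
|---|---|---|---|
| Statistical analysis | 2 | half the sample at 4 weeks, then at 8 weeks | not stated there |
| Experimental group | 2 | 4 and 8 weeks | unblind, prophylaxis for both groups |
| Ethical considerations | 2, plus the end of 3 months | week 4, week 8 | amendment to unblind |
| DSMC | 1 | half completed, or half recruited | stop for benefit |

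Treatment lasts 60 days (about 8.6 weeks), so half completed could roughly match the 8-week look. The 4-week look matches neither DSMC trigger.

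**2. Inputs for the error rate**

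- From the protocol: two-sided 5%, log-rank test, 76% COVID-free on placebo and a 10-point gain, hence 24% and 14% events.
- Assumed: every look is tested at |Z| > 1.96; the information fractions; uniform accrual over 0 to 22 weeks; constant hazard; average event rate (24% + 14%)/2 = 19%.

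**3. Formula**

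With no effect, the log-rank statistics at information fractions t1 < t2 < … < 1 are approximately multivariate normal with mean 0 and correlation √(ti/tj). Overall type I error = 1 − P(|Zi| ≤ 1.96 at every look).

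**4. Results with |Z| > 1.96 at every look**

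- Final analysis only: 5.0%, the protocol's stated level.
- One interim at t = 0.5 plus final (correlation √0.5 = 0.71): **8.3%**.
- Two interims at 1/3 and 2/3 plus final: **10.7%**. At 0.35 and 0.67: **10.6%**.

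**5. Fractions derived for the 4- and 8-week looks**

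With weekly hazard λ = −ln(0.81)/F for follow-up F in weeks, and everyone entering at once, t(w) = (1 − e^(−λw))/0.19.

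- F = 13 (three months): λ = 0.0162, t(4) = 0.33, t(8) = 0.64, error 10.8%.
- F = 60/7 = 8.57 (60 days): λ = 0.0246, t(4) = 0.49, t(8) = 0.94, error 9.2%.
- Accrual spread over 4 to 22 weeks: 10.4 to 10.8% for F = 13, and 9.3 to 9.8% for F = 8.57.

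The range is therefore about 9 to 11%. Other assumed spacings give 10.1% (0.30 and 0.90) to 12.0% (0.15 and 0.30).

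**6. Sensitivity of the one-interim figure**

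Over the same accrual and follow-up scenarios, half completed gives 5.0 to 7.6% and half recruited gives 8.9 to 9.75%. The 8.3% is the value at half the information.

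**7. With a boundary**

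- Haybittle-Peto, |Z| > 3.29 (p < 0.001) at both interims and 1.96 at the end, looks at 0.35 and 0.67: about 5.05%.
- O'Brien-Fleming at 1/3, 2/3 and 1: nominal two-sided levels 0.0005, 0.0141 and 0.0451, overall 5%.
- O'Brien-Fleming with one interim at 0.5: 0.0052 and 0.048.

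**The case against.** The strongest reply is that no section says any interim is tested at 5%. That level stands under the sample-size heading. The wording about magnitude and clear benefit suggests a higher bar for acting early, and Ethical considerations describes unblinding as an amendment to be proposed. Boundaries are often left to a statistical analysis plan, which may exist and is not shown, and the DSMC section does state an intention to account for the interim.

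Much of this stands. A reader might infer that the trial's false-positive rate is double the nominal 5%. The documents do not support that as a fact: the interim criterion is undefined, not shown to be 5%, and about double fits only the two-interim schedule.

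A reader might also combine all the looks, which gives about 12 to 15%. No section says that both schedules are run. Nor can one say that the DSMC look would hold very few events: that follows only from the half-recruited wording and an assumed accrual rate, while the sentence that plans the interim says completed.

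Finally, a reader might conclude that crossed-over placebo time will bias the hazard ratio toward 1. The protocol does not say that such time is retained; its handling is simply not stated.

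What the reply does not answer is the contradiction. A separate analysis plan cannot make protocol sections with different numbers of looks and different triggers agree. The promised adjustment speaks of one look where Statistical analysis plans two.

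**Conclusion.** The point holds in this form: the interim schedules contradict each other, and looks that can open the blind or stop the trial for benefit have no stated criterion beside a single two-sided 5%. This rests on the protocol's own text and needs no assumption.

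The size is conditional. If each look were tested at 5%, overall type I error would be about 8% with one interim at half the information and about 9 to 11% with two interims, or up to 12% if both come very early. Accrual and information fractions are assumptions throughout. On the half-completed reading with very fast accrual, the single interim nearly coincides with the final analysis and the inflation almost vanishes.

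The contradiction should be settled before any interim data are seen, because an early unblinding cannot be reversed.

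**What to change.** 1. Reconcile Experimental group, Statistical analysis, DSMC and Ethical considerations to one interim schedule with one trigger per look, for example the two follow-up-based looks.
2. State, or refer explicitly to the statistical analysis plan for, an efficacy boundary for the planned log-rank test that holds overall alpha at about 5%. Haybittle-Peto (p < 0.001 at interims, 0.05 at the end) or an O'Brien-Fleming-type spending function on the event fraction would each do. Make the sentence about accounting for the interim cover every planned look.
3. State that, if the blind is opened and placebo subjects are offered HCQ, the primary randomised comparison uses data up to the unblinding date.

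The cost is wording in the protocol and the committee's instructions. Under Haybittle-Peto the final test stays at 0.05, so final power is essentially unchanged; with O'Brien-Fleming at thirds the final level falls to about 0.045. The downside of either is a lower chance of stopping early for benefit.
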